### Harms

2.16

Both groups of participants will make records during each treatment session in order to collect, evaluate, report and manage the potential adverse effects of the intervention in the study. According to informed consent, patients with increased symptoms after the treatment will be immediately evaluated by the TMJ specialists.

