#### Experiment group

2.6.2

The experimental group will perform CBT on the basis of the control group. The CBT in this study will mainly be implemented by therapeutic meetings. The intervention times are the first visit and the second visit (the first and second weeks after the first visit), a total of three times, each meeting last about 30 minutes. The specific intervention steps and methods are as follows:

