
**Table 1 T1:** Checklist of CBT on TMD patients.

Intervention process	Intervention time	Intervention goal	Intervention content
The first stage	First visit	To establish a good relationship with the patient; cognitive assessment	①Understand the degree of kinesiophobia of the patient; ②Understand the relevant risk factors that cause kinesiophobia in patients; ③Provide WeChat QR code to facilitate patients to obtain TMD related knowledge; ④Establish short-term and long-term exercise goals based on the patient's terrorism and cognitive and cultural level.
The second stage	One week after the first visit)	Review the last conversation and get the latest news of the patient; correct unreasonable cognition	①Discover unreasonable disease thinking and cognition, and promptly correct the patient's “wrong cognition of thinking about kinesiophobia”; ②Explain the benefits of early joint exercises to patients; ③Encourage patients to overcome their kinesiophobia and continue to accomplish their goals.
The third stage	Follow-up consultation	Cognitive reconstruction	①Check the completion of the patient's rehabilitation goals and improve the exercise plan; ②Check the patient's mastery of relaxation training, find out the existing problems and give corrections and guidance; ③Encourage patients to perform rehabilitation exercises according to health education manuals and videos.
Follow-up	1, 3, and 6 month after the end of the intervention		①Regularly push TMD-related knowledge and how to protect the TMJ to patients through WeChat groups; ②The patients were followed up once a week in the first month after the intervention, every two weeks in the second to third months, and once a month in the fourth to sixth months, and patients were regularly asked about the improvement of pain and the recovery of mandibular function.

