### Outcome measures

2.7

The primary outcomes and secondary outcomes will be collected in 4 time points: before intervention, 1 month after intervention, 3 month after intervention, 6 month after intervention. All variables will be measured in both experiment group and control group.

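### Adverse-effect recording is tied to an undefined treatment session, so recording occasions differ between arms and none is stated for the 1-, 3- and 6-month follow-up

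*Protocol article*

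**What the plan says.** Section 2.16 (Harms) has two operative sentences. The first sets when adverse effects are recorded: "Both groups of participants will make records during each treatment session in order to collect, evaluate, report and manage the potential adverse effects". The second concerns care: "patients with increased symptoms after the treatment will be immediately evaluated by the TMJ specialists".

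Section 2.6.2 (Experiment group) places the CBT meetings at the first visit and at "the first and second weeks after the first visit), a total of three times". Table 1 dates the third stage only as "Follow-up consultation", without a week. Both then list follow-up to six months as a separate stage after the intervention has ended. The third session closes by encouraging patients to carry on at home with the manuals and videos.

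Section 2.6.1 (Control group) describes conventional treatment, including jaw exercises, with no visit schedule, and says that the trial will not try to steer patients' dental care. The CBT arm receives this treatment too.

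Section 2.7 (Outcome measures) has the primary and secondary outcomes in both arms "collected in 4 time points: before intervention, 1 month after intervention, 3 month after intervention, 6 month after intervention". It does not mention adverse effects. The follow-up row of Table 1, which is the CBT checklist, says that "patients were regularly asked about the improvement of pain and the recovery of mandibular function".

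**The concern.** Comparing harms between arms requires that participants in both arms are asked the same thing, equally often, over the same period. A rule based on sessions does not secure this when one arm has extra sessions by design and the other has no stated schedule.

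Two distortions can follow, and they need not cancel. More recording occasions early on can raise the count in the CBT arm for no reason but more frequent asking. And if nothing is recorded systematically after the sessions, both arms may report few events from the months in which patients exercise without supervision. The CBT programme sets out to increase movement of a painful joint in patients who avoid moving it, so readers will want a tolerability statement they can rely on. The efficacy comparison is not affected.

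**Working it through.** The protocol gives no harms figure to reproduce. The check sets the sections side by side and counts occasions.

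**Step 1: what a treatment session could mean.** Let *d* be the number of conventional-treatment visits per patient. It is not stated for either arm.

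| Reading | CBT arm | Control arm | Consequence |
|---|---|---|---|
| CBT sessions only | 3 | 0 | Contradicts section 2.16, which covers both groups |
| CBT sessions and conventional visits | 3 + *d*(CBT) | *d*(control) | Difference = 3 + *d*(CBT) − *d*(control) |
| Conventional visits only | *d*(CBT) | *d*(control) | Not fixed; depends on dental care |

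The second reading fits best, because section 2.6.2 calls the CBT meetings sessions and section 2.16 includes controls. With equal numbers of conventional visits, the difference is 3 + *d* − *d* = 3. If some CBT sessions fall on the day of a dental visit, the excess in separate days is smaller, so up to three is the fair statement. No reading fixes an equal number of occasions.

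**Step 2: is follow-up a treatment session?** Section 2.6.2 numbers Sessions 1 to 3, declares the intervention ended, and then lists follow-up. Table 1 makes the same split. In the document's own terms, the 1-, 3- and 6-month assessments are not sessions. An adverse-effect record is stated at 0 of these 3 assessments.

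**Step 3: could the interim contacts serve instead?** Table 1 has them weekly in month 1, two-weekly in months 2 and 3, and monthly in months 4 to 6.

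- At 4 weeks per month: 4 + 8/2 + 3 = 11.
- At 4.35 weeks per month: 4.35 + 8.70/2 + 3 = 11.7.

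That is 11 to 12 contacts in the CBT arm. None is stated for controls. Used to capture harms, they would raise the CBT arm's additional occasions from 3 to 14 or 15 (3 + 11 or 3 + 12), against none stated for controls.

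**Step 4: what would the scheduled scores show?** The NRS gives a pain level. The OHIP-TMDs covers limited function, physical pain and physical disorder, among other dimensions. Both would reflect some worsening in both arms. Neither records that an event happened, what it was, or when. Section 2.10 lists joint locking and limited mouth opening from the case book but gives no time points.

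**The case against.** The strongest reply is that a two-sentence harms section in a journal article is a condensation, and that adverse-event forms and schedules usually sit in the full protocol, which is not shown. That would answer a complaint about silence. It does not answer a stated rule: section 2.16 says when records are made, and that rule gives unequal occasions.

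A reader might go further and infer that harm recording in the CBT arm stops after about two weeks and that later harms are lost. The document does not support that:

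- Section 2.16 does not say that recording is confined to sessions.
- It covers both groups, so conventional visits must count. The CBT arm has these too, on an unstated schedule, and recording could run well beyond week 2.
- Table 1 does not date the third session.
- Patients with worsening symptoms are seen by specialists, and CBT patients can reach the team by WeChat.
- The interim contacts, the NRS and the OHIP-TMDs could all reveal deterioration.

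For the same reasons, a proportion of follow-up time covered, or an expected number of missed events, cannot be derived. Either would need a two-week window that is not established and event risks that the document does not give.

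It is also fair to say that jaw exercise belongs to conventional treatment in both arms, so exercise-related harm is not peculiar to CBT. That stands. It makes equal ascertainment more important, because the question becomes whether CBT adds harm to a background present in both arms.

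**Conclusion.** The point holds in a limited form. The only stated recording occasion is a treatment session, which is not defined by arm. The CBT arm has up to three more such occasions by design, assuming similar numbers of conventional visits in the two arms. No adverse-effect record is stated at any of the three follow-up assessments. The contacts that might fill the gap number 11 to 12 in the CBT arm and none stated in the control arm, and they are framed around improvement and recovery.

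The document does not establish that later harms would be missed. It establishes that their capture is not fixed and is not equal between arms. The direction of any bias in the harm comparison cannot be determined from what is stated. The conclusion rests on reading follow-up as distinct from sessions, as section 2.6.2 and Table 1 both do. If the full protocol already provides the same recording to month 6 in both arms, only the wording of section 2.16 needs correcting. The change is worth making because it is cheap, not because the trial's main conclusion is at risk.

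**What to change.** - In section 2.16, define treatment session for each arm and keep the session records.
- Add one identical short adverse-effect item (yes/no, with date) to the 1-, 3- and 6-month questionnaires in both arms.
- Report the number of participants with any event per arm over the same fixed window from randomisation to month 6. Date the window from randomisation in both arms, because controls have no last CBT session to count from.
- Do not use the Table 1 contacts for the between-arm harm comparison unless the same contacts are made in the control arm.
- Reconcile the third-session timing in section 2.6.2 with Table 1.

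The cost is a few lines on questionnaires that both arms already complete, and a notification to the Ethics Committee, which section 2.17 already requires for changes to the plan. No visits are added and no treatment changes.

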### Ethics

2.17

The study will be conducted under the Declaration of Helsinki principles and standardized clinical practice. This study protocol has been approved by the Ethics Committee of Stomatological Hospital of Tianjin Medical University, with the reference number TMUhME2019001. The study has been registered in the Chinese Clinical Trial Registration Center with the number ChiCTR2000038573. If there is a need to modify this plan, the researchers need report to the Ethics Committee immediately. Participants need to acknowledge that they have participated in this study.

## Discussion

3

Due to lack of research measurements and language limitation, the current studies mainly focus on epidemic, animal experiments in china. However, there is few studies conducted psychological behavior intervention on TMD patients, especially using kinesiophobia as the main outcome. To the best of our knowledge, this will be the first randomized controlled trial that we conduct a psychological intervention on Chinese TMD patients by using kinesiophobia and oral health related quality of life as primary outcomes to explore the effectiveness of CBT. The participants will be divided into experiment group and control group. The control group will receive a conventional treatment, whereas the experimental group will receive CBT on the basis of the control group. In previous studies, Cai et al^[35]^ conducted CBT on kinesiophobia to patients after total knee arthroplasty, kinesiophobia is significantly reduced after intervention, which ensured the amount of rehabilitation training for patients and promoted the recovery of knee function. Archer et al^[49]^ implemented CBT on patients after lumbar fusion surgery, and the results demonstrated that CBT can reduce kinesiophobia, as well as pain disability, the quality of life has also been significantly improved. However, the lack of individual or group treatment programs, the effectiveness of CBT for chronic pain is difficult to reach a definite conclusion.^[50]^

In previous studies, the efficacy of CBT in TMD patients has been explored, but most of these studies use pain intensity as a primary outcome, the duration of the effect has not been determined. The reason may be that there are great differences in CBT studies for TMD patients, including specific techniques, different background of the implementers, treatment frequency, treatment time, observation time after treatment, etc.^[51–55]^ In the study of the effectiveness of CBT alone, Mishra et al^[56]^ reported that patients in the CBT group had lower pain intensity compared to the non-treatment group, Gardea et al^[57]^ also reached the same conclusion. Dworkin et al^[52]^ reported that after 6 courses of CBT treatment, the patient's pain did not significantly improve compared with the conventional treatment group. Mishra et al^[56]^ performed more frequent CBT (12 courses of treatment) on patients without any mental disorders, and the pain intensity was significantly reduced. Tuner et al^[34]^ showed that CBT significantly improved the pain intensity in the 12-month follow-up, but haven’t been improved in the 8-week follow-up. These indicate that the intervention time and follow-up time need to be considered in the process of CBT.^[34,55]^

Through literature review, we found that the previous protocols of CBT mainly focused on the improvement of the negative emotions, such as anxiety, depression, and pain management, whereas our study focus on improving the patient's kinesiophobia, with the goal of improving patients’ quality of life. We correct the patient's poor cognition of the fear of mandibular movement, so that the patient can actively treat and exit the cycle of false cognition.

In addition, considering that the ability of CBT implementers may affect the patient's prognosis, the implementers of our research team will be trained by psychotherapists before the intervention. It will be carried out under the premise of comprehensively considering the patient's psychological status, disease severity, and treatment frequency.

To enhance the reliability of the results, methodological factors will be considered in our study. Taking the possible absence and withdrawal of the subjects into consideration, the sample size has been increased by 20%. If there is any missing or withdrawal of the participants, statistical analysis will be conducted according to the research protocol and intention-to-treat analysis.

Diagnostic and statistical manual of mental disorders (DSM)^[58]^ and international classification of diseases (ICD)^[59]^ has been recommended for psychiatric diagnosis. These manuals may contribute to the diagnosis of Axis II in TMD patients and the implementation of psychosocial interventions. However, the diagnostic criteria for Axis II are not widely used in China, and there are no clinical studies providing psychosocial treatment for TMD patients. However, the importance of axis II diagnosis and psychosomatic intervention should be recognized in managing TMD pain. Therefore, the clinical collaboration between TMD specialists and psychologists is essential to manage TMD.

It should be mentioned that the study has some limitations. First, this study will be only conducted in a specialized stomatological hospital with limited sample size, large sample size and multi-center randomized controlled trials can be carried out to verify the reliability of our study. Second, the outcomes of the study are mainly measured by self-report questionnaires. However, the differences generated by objective indicators are relatively small. Third, the study will only conduct CBT program, further research could combine exercise intervention, mindfulness intervention and other multi-component intervention treatment to explore the effects on kinesiophobia and OHRQOL in patients with TMD.

The study is a randomized controlled trial that aims to explore the CBT on kinesiophobia and OHRQOL in patients with TMD. The research results would provide supplements for the treatment and management of kinesiophobia, as well as provide evidence for controversial topics in TMD patients with CBT treatment.
